### Behavioural intervention

The study is powered for the cross-over RCT, rather than for the behavioural support intervention. Therefore, in line with the MRC guidance for developing complex interventions,^36^ the aim of this secondary aspect of the study is to explore the feasibility and acceptability of the behavioural support intervention to reduce UPF (primary target behaviour) and increase physical activity (PA) (secondary target). Full details of the intervention development and content will be provided in a future publication focused on the behavioural support intervention. The exit interview guide is provided in online supplemental material 4. However, in brief, the intervention was developed following the steps outlined in the Behaviour Change Wheel framework for intervention development,^37^ which incorporates the ‘Capability, Opportunity, Motivation’ model for understanding behaviour (COM-B), augmented with Theoretical Domains Framework (TDF) for using behaviour change theory.^36 38^ Qualitative studies of barriers and facilitators for dietary change in healthcare workers were extensively reviewed, with findings then mapped onto the TDF, and behaviour change techniques (BCT) consistently associated with successful diet and PA change drawn from meta-analyses of RCTs.^39–41^ The intervention content combines monthly video/telephone behavioural support calls with print/online resources, based on TDF domains. Some examples of TDF domains (linked to the intervention components) are knowledge (information on what UPFs are and how to recognise them), environment (mapping of food outlets local to participant’s workplace to for quickly accessible MPF options), beliefs about consequences (information about links between UPF and health), behavioural regulation (support with goal-setting, action-planning, self-monitoring, habit) and social influence (moderated online peer support sessions). The calls will be individually tailored based to participant demographics/work patterns, responses to their baseline COM-B questionnaire, baseline levels of UPF intake and reported PA (measures of these are all described in the outcomes section) and personal barriers and motivations to change.

10.1136/bmjopen-2023-079027.supp4Supplementary data

### Outcomes

Outcome measures will be collected at seven in-person visits. See figure 1 and online supplemental material 5 for the schedule of assessments.

10.1136/bmjopen-2023-079027.supp5Supplementary data

The primary outcome is the mean difference in percent weight change (%WC) at 8 weeks from baseline between MPF and UPF diets. This outcome is currently being used clinically in weight management clinics and used for all NHS weight management programmes. Clinically significant weight change can occur from short-term dietary interventions and directly relates to improvements in cardiometabolic risk factors (eg, blood pressure, blood glucose, glycated haemoglobin (HbA1c), lipids),^42^ physical function and quality of life.^43^ Weight is an efficient and more accurate measurement to collect than other energy balance measures, such as energy intake. The hypothesised %WC in the face of the current growing obesity pandemic would have clinically relevant impacts on halting the rate of progression of obesity prevalence and mitigating the adverse impacts of adiposity-related disease, simply through shifts in the types of processed in foods being consumed.

Secondary outcomes include changes in dietary intake, waist circumference, body composition (fat mass, fat-free mass), heart rate, blood pressure, cardiometabolic risk factors (comorbidities and blood biomarkers including liver function, lipid profile, glucose, HbA1c and C reactive protein), fasted and fed metabolomics, appetite measures (fasted and fed appetite scores, circulating gut hormones and adipocytokines), sleep, sleep quality, PA levels, physical function (walking distance, leg strength, handgrip strength), mental health, quality of life, well-being and aspects of eating behaviour between MPF and UPF diets, and after the 6-month behavioural intervention compared with the first baseline assessment. In a subset of participants, changes in brain functional resting state connectivity between MPF and UPF diets will be assessed. Further behavioural intervention secondary outcomes include understanding the experiences of UPF versus MPF diets, changes in behaviour regulation and shopping expenditure from the first baseline assessment, and barriers and facilitators to reducing UPF intake.

Meal tests with blood samples for biomarkers, metabolomics, gut hormones and adipocytokines will be collected at five visits: baseline visits and 8 weeks follow-ups for the RCT and at 6 months follow-up for the behavioural intervention. A random subset of participants will undergo MRI scans at four visits: baseline visits and 8 weeks follow-ups for the RCT. The COM-B behaviour change questionnaire will be assessed at two visits: the first baseline visits and at 6 months follow-up.

### Participant timeline

The trial duration per participant is 49 weeks (see figure 2). The overall trial is expected to last 24 months. Recruitment commenced in March 2023 and is expected to continue until March 2024 or when 55 participants have been recruited.

**Figure 2 F2:**
[figure not shown]
Participant timeline.

## Methods: assignment of interventions

### Randomisation

Enrolled participants will be block randomised (stratified by night shift status, sex and ethnicity as potential treatment modifiers) to receive: (1) the MPF diet then UPF diet or (2) UPF diet then MPF diet. Randomisation will be performed using Sealed Envelope by the research team (https://www.sealedenvelope.com).

The trial statistician, but not researchers, will be blinded to the diet assignments. To prevent bias, participants are informed that the provided interventions are healthy balanced diets made with different types of food processing. All participant communications omit the terms MPF/UPF, with diets instead being referred to generally as diet 1/A or diet 2/B. Unblinding procedures are not required.

## Methods: data collection, management and analysis

### Data collection methods

#### Sociodemographics

Age, gender, ethnicity, occupation, work pattern, educational level, marital status, medication intake, alcohol consumption, smoking habits, family history of obesity, cardiovascular disease and diabetes will be collected at screening.

#### Anthropometrics and body composition

Weight will be measured using an electronic scale to the nearest 0.1 kg (Tanita DC-430MAS; Tanita, Tokyo, Japan). Body composition including fat mass, fat-free mass and bone mass will be assessed using bioelectrical impedance analysis (Tanita) at each visit. Height will be determined using a stadiometer to the nearest 0.5 cm and body mass index derived from weight and height (in kg/m^2^). Waist circumference will be measured using a non-stretch tape measure at the iliac crest.^44^

#### Vital signs

Blood pressure will be recorded in triplicate, seated, alongside heart rate with an automated sphygmomanometer and oximeter.

#### Mixed meal test and blood samples

Mixed meal tests will be used to assess circulating gut hormones, adipocytokines and metabolomics, given the significant differences in metabolites and appetite hormones between UPF and MPF diets in.^21 21^ Participants will consume 187.5 mL Ensure Compact 2.4kcal (https://nutrition.abbott/uk/product/ensure-compact) after an overnight fast. Fasted blood samples taken before the test include venous glucose, HbA1c, liver function tests, lipid profile and C reactive protein, relevant for cardiometabolic health. Blood samples and subjective appetite assessments using a Visual Analogue Score will be collected immediately before, and 15 and 30 min after starting the liquid meal.^45^ Fasted and postprandial circulating appetite hormones (ghrelin, peptide YY and glucagon-like-peptide-1), adipocytokines as markers of adipose tissue inflammation (leptin, resistin, adiponectin, interleukin-6 and tumour necrosis factor alpha) and metabolomics analysis of 250 metabolites using the Nightingale platform (https://nightingalehealth.com) will be collected and stored at −80°C.

#### PA levels and sleep quality

PA levels will be measured objectively using accelerometry (ActiGraph wGT3X-BT). The device has been previously used in clinical research given its practicality, non-invasiveness, and reliability and accuracy in measuring PA in free-living adults.^46^ Data recorded includes energy expenditure, metabolic equivalents and sleep activity. The short-form International Physical Activity Questionnaire (IPAQ-SF) will be used to subjectively assess light, moderate and vigorous PA, and time spent sitting.^47–49^ The IPAQ-SF contains seven questions about PA in the past 7 days.^50^ ActiGraph wGT3X-BT will also objectively measure sleep quality and quantity. The Pittsburgh Sleep Quality Index (PSQI) is a validated 19-item measure for determining sleep quality in the past month, to distinguish between good and poor sleepers.^51^

#### Physical function and strength

Static muscle strength of the upper extremities will be assessed using a handgrip dynamometer (Jamar Hydraulic Hand Dynamometer, Patterson Medical). Three measures will be recorded (in kg) with each hand, alternately, while seated. Functional capacity will be assessed using the 6 min walk test, a self-paced submaximal assessment, validated in people living with obesity.^52^ The test will be performed according to the ‘*American Thoracic Society Statement: Guidelines for the Six-minute Walk Test*’ protocol.^53^ The pretest and post-test heart rate, total distance covered, perceived physical exertion and any physical problems will be recorded. Lower body functional capacity will be assessed using the sit-to-stand test.^54^ Participants will be requested to perform five sit-to-stand repetitions as fast as possible with arms crossed over the chest. The number of repetitions and time to completion will be recorded.

#### Quality of life, mental health and well-being questionnaires

EuroQol 5-Dimensions 3-Levels (EQ-5D-3L) is a 6-item questionnaire containing a descriptive system assessing five domains: mobility, self-care, usual activities, pain/discomfort and anxiety/depression using three levels (eg, mobility: I have no problems walking about, I have some problems walking about or I am confined to bed) and a visual analogue scale reporting self-rated health from 0 to 100.^55^ Impact of Weight on Quality of Life-Lite (IWQOL-Lite) is a 31-item, obesity/overweight-specific measure of health-related quality of life relating to five domains: physical function, self-esteem, sexual life, public distress and work. Higher scores indicate a better quality of life.^56^ The Warwick Edinburgh Mental Well-being Scale (WEMWBS) is a 14-item, positively worded, validated measure of mental well-being. Five responses are summed for a total score between 14 and 70, with higher scores indicating greater positive mental well-being.^57^ The Patient Health Questionnaire (PHQ-9) is a nine-item validated measure to assess the severity of depression.^58^ Each item is rated from 0 to 3, for a total score out of 27. A score of 1–4 indicates minimal depression, 5–9 indicates mild, 10–14 indicates moderate, 15–19 indicates moderately severe, with 20–27 indicating severe depression. The Generalised Anxiety Disorder assessment (GAD-7) is a seven-item anxiety scale to measure the severity of GAD.^59^ Each item is rated from 0 to 3, for a total score out of 21. A score of 11–15 indicates moderately severe anxiety, with 16–21 indicating severe anxiety.

#### Eating Behaviour Questionnaires

The Power of Food (PoF) scale is a 15-item validated measure to assess the psychological impact of living in food-abundant environments.^60^ The Control of Eating Questionnaire (CoEQ) is a 21-item validated measure of the severity and type of food cravings.^61^

#### Behaviour Change Questionnaire

Participants will complete a questionnaire investigating the barriers and facilitators to PA and healthy eating based on COM-B.^62^ The PA component contains 137 items, and the eating component contains 120 items.

#### MRI

Several aspects of UPFs may influence eating behaviour, including changes to the food composition, food matrix degradation and behavioural aspects, including large portion presentation, cost, availability, shelf life, heavy marketing and attractive packaging.^16^ UPFs have been suggested to have addictive-like properties,^63^ evoking strong emotional reactivity from visual cues.^64^ Functional brain MRI has provided valuable insights into appetite regulation,^65^ and how obesity impacts the neurobiology of weight regulation. However, the neurobiological impact of high-UPF diets is largely unknown. A subset of participants (n=24) will undergo an advanced MRI brain protocol at the baseline and 8-week visits of the RCT (four visits), to assess a number of changes in brain properties: (1) functional resting-state connectivity between regions implicated in eating behaviour, metabolism and swelling linked to diffuse inflammation, and their reversibility^66^; (2) microstructure brain properties extracted from diffusion weighted imaging data^67^; (3) changes in brain dynamics, based on each subject’s functional and structural connectivity^68^; (4) metabolite changes, such as glutamate, N-acetyl aspartate and Inositol, through brainstem MR spectroscopy^69^; (5) regional volume changes through high-resolution structural scans^66^ and (6) relaxometry properties alterations affected by inflammation.^70^

#### Assessment of dietary adherence and intake

In line with previous trials,^71^ multiple approaches will be used to assess dietary intake and adherence, including 24-hour recalls, food frequency questionnaires (FFQ) and image-based dietary assessment (IBDA).

Intake24^72^ is a validated, online, self-reported 24-hour recall system, based on a multiple-pass recall suitable for the general population^73 74^ (https://intake24.co.uk). The web-based recall method is convenient, efficient and ensures coding consistency. Participants enter all food and drink consumed in the previous 24 hours (from waking up to going to sleep) into Intake24 on two non-consecutive days per visit period. Each recall takes roughly 12 min to complete.^75^ The first recall at screening will be conducted with the research team to ensure adequate training. Links will then be sent to participants to complete further recalls remotely. Intake24 is connected to the National Diet and Nutrition Survey Nutrient Databank to provide nutrient outputs and has been coded into NOVA by the research team for calculating UPF/MPF intake.^76^ Intake24 includes details on the brand names of products, facilitating assignment of NOVA groups.

The European Prospective Investigation into Cancer and Nutrition (EPIC)-Norfolk FFQ is a validated, semiquantitative measure of average dietary intake over the past year.^77–79^ The FFQ contains a 130-item food list followed by detailed questions regarding the food list. For each food item, participants tick the most appropriate frequency of consumption of that item from nine options (from never or less than once per month, to 6+ per day).

Participants will complete an FFQ and two non-consecutive day 24-hour dietary recalls at baseline, and 4 weeks and 8 weeks for both diets and at the 6-month behavioural intervention follow-up (figure 1).^80^ IBDA will also be completed on two non-consecutive days during weeks 4 and 8 of the RCT, whereby participants will take photos before and after their ad libitum meals/snacks.

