### Interventions

Eligible participants will receive in a random order (1) an 8-week MPF diet (at least 80% MPF (NOVA group 1), <20% UPF) and (2) an 8-week UPF diet (at least 80% UPF, <20% MPF), both following EWG recommendations. During the 4-week washout between diets, participants will return to their habitual diet to minimise carryover effects.

Participants will be given all meals, snacks and drinks for each 8-week intervention to maximise adherence, ensure internal validity and minimise dropout.^30 31^ Catering companies and supermarkets will deliver diets to participants’ homes, two times per week. Deliveries will be scheduled according to participants’ convenience.

Both diets will follow EWG recommendations, choosing foods with green or amber front of package traffic lights for total fat, saturated fat, sugar and salt over foods with red traffic lights, consuming five portions per day of fruit and vegetables, and eating a variety of foods in the right proportions.^18^

Diets will be matched for and aim to follow government recommended intakes for a 2000kcal/day diet^4 18^ (table 3). Provided diets will be scaled up to 4000 kcal/day, to ensure participants are not energy restricted and energy intake is ad libitum.

**Table 3 T3:** Eatwell Guide dietary recommendations^4 18^

Component	Guidance
Total fat	35% of provided energy intake or below, 78 g or less/2000 kcal
Saturated fat	10% of provided energy intake or below, 24 g or less/2000 kcal
Salt	Less than 6 g per day. Intake in line with current UK average intakes,^94^ aiming for below 6 g per day
Carbohydrate	Around 50% of provided energy intake, 267 g/2000 kcal
Total sugars	Less than 90 g/2000 kcal, less than 18% of total energy
Protein	Around 15% of provided energy intake, 45 g/2000 kcal
Fibre	At least 18 g/2000 kcal
Fruit and vegetables	Five portions per day

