The menus will be designed to be representative of UK diets, by identifying the most commonly consumed foods in the UK National Diet and Nutrition Survey.^32^ Practical and logistical aspects including price, best-before dates, storage requirements and accessibility will be factored into the design. Diets will be matched where possible, with MPF/UPF versions of the same meals (eg, Caesar salad, salmon and potatoes, porridge/breakfast cereal). UPF items are typically foods obtained from supermarkets, whereas MPFs are freshly made culinary preparations. The menu will vary across the week to prevent participant boredom and sensory-specific satiety,^33^ but repeating each week to allow consistency and reduce burden. Alcohol will not be provided. Participants will be asked to keep alcohol consumption within government guidelines (≤14 units per week).^34^ Participants will be educated on the EWG, but further lifestyle guidance will not be given. Menu guides will be provided with instructions and pictures to prepare each meal. As in previous ad libitum feeding trials investigating weight change,^35^ participants will be asked to consume as much or as little of the provided diets as they desire, but they will not be asked to actively reduce their energy intake.

Participants will receive weekly calls from the research team, including dietitians, to discuss any issues with the diets and to promote adherence. Participants will have a food diary to track adherence and to record any food consumed off diet. The 4-week and 8-week diet assessments will also be used for monitoring adherence. Participants will be encouraged to report any deviations from the provided diets during weekly calls and in the food diary and to be as honest as possible, with no repercussions. Previous studies indicate high adherence when all food is provided and delivered to participant homes, where eating foods provided is more of a challenge than eating foods off the diet.^30^ Minor modifications to the intervention that do not alter the overall design will be acceptable for enabling adherence. For example, adding herbs or spices (without sugar/salt) to taste or providing alternative items to facilitate food preparation if participants do not have access to a microwave (eg, swapping a microwaveable meal for a ready-to-eat meal).

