#### Questionnaires summary

There are 12 questionnaires/surveys: PSQI, IPAQ-SF, EQ-5D-3L, IWQOL-Lite, WEMWBS, PHQ9, GAD7, PoF, CoEQ, COM-B healthy eating and PA questionnaire, Intake24 and EPIC-Norfolk FFQ. Time points for completion are detailed in table 4 and in online supplemental material 5.

**Table 4 T4:** Time points of questionnaires in the UPDATE trial

Visit	No of questionnaires	Time to complete
Screening	Intake 24 only	12 min
RCT: First baseline visit Behavioural intervention: 6 months follow-up (visits 2 and 9)	All 12 questionnaires	90 min
RCT: Week 4 Week 8 Second baseline visit (visits 3, 4, 5, 6 and 7)	11 questionnaires (all except the COM-B healthy eating and PA questionnaire)	60 min

COM-B, Capability, Opportunity, Motivation-Behaviour; PA, physical activity; RCT, randomised controlled trial; UPDATE, Investigating the effects of Ultra-Processed versus minimally processed Diets following UK dietAry guidance on healTh outcomEs.

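### The food frequency questionnaire covers the past year but is used at weeks 4 and 8 of each diet, so its intake and adherence results will be heavily diluted

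*Protocol article*

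**What the plan says.** The section on assessment of dietary adherence and intake states that "multiple approaches will be used to assess dietary intake and adherence, including 24-hour recalls, food frequency questionnaires (FFQ) and image-based dietary assessment (IBDA"). It describes the FFQ as a "validated, semiquantitative measure of average dietary intake over the past year". The schedule follows: "Participants will complete an FFQ and two non-consecutive day 24-hour dietary recalls at baseline, and 4 weeks and 8 weeks for both diets", with a further round at the 6-month follow-up.

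Table 4 agrees. Week 4, week 8 and the second baseline carry "11 questionnaires (all except the COM-B healthy eating and PA questionnaire"), and the FFQ is one of those 11. The Interventions section adds: "The 4-week and 8-week diet assessments will also be used for monitoring adherence". Under Outcomes, diet is a named endpoint: "Secondary outcomes include changes in dietary intake, waist circumference, body composition".

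Nothing in the article shortens or adapts the FFQ's recall period.

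**The concern.** The instrument, its recall window, its schedule and its purpose are all stated, and they do not fit together. A questionnaire about average intake over a year is asked to describe a diet that has lasted four or eight weeks. Other questionnaires with a stated window fit the schedule: the IPAQ-SF covers seven days and the PSQI one month.

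At stake is one measure of a secondary outcome and one source of adherence information. Read alone, the week 8 FFQ of a fully adherent participant would show little change. It could then seem to contradict the recalls, photographs and food diary, which do match the diet periods.

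**Working it through.** The plan gives no figure of its own to reproduce here. The check is how much of a 52-week window each diet occupies at each FFQ visit.

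**Inputs.** The window is 52 weeks, from the past-year description. Each diet lasts 8 weeks. The washout lasts 4 weeks on habitual food: "During the 4-week washout between diets, participants will return to their habitual diet to minimise carryover effects". Diet 1 therefore runs over weeks 0–8, washout over weeks 8–12 and diet 2 over weeks 12–20.

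**Assumptions.** The question is answered literally, with equal weight on every week. Intake is stable within each diet, and equals the habitual level before the trial and during washout.

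**Weeks in the window**

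| FFQ visit | Current diet | Other provided diet | Habitual | Share on current diet |
|---|---|---|---|---|
| Diet 1, week 4 | 4 | 0 | 48 | 4/52 = 7.7% |
| Diet 1, week 8 | 8 | 0 | 44 | 8/52 = 15.4% |
| Second baseline | – | 8 (diet 1) | 44 | – |
| Diet 2, week 4 | 4 | 8 | 40 | 4/52 = 7.7% |
| Diet 2, week 8 | 8 | 8 | 36 | 8/52 = 15.4% |

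**Change from period baseline.** Let h be the habitual mean of any intake quantity, and U and M its means on the ultra-processed and minimally processed diets. Let D1 and D2 be the means on the first and second diet.

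- Period 1, week 8: (44h + 8·D1)/52 − h = 8(D1 − h)/52.
- Period 2, week 8: (36h + 8·D1 + 8·D2)/52 − (44h + 8·D1)/52 = 8(D2 − h)/52.

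The first diet cancels in period 2. In both periods the between-diet difference in change is 8(U − M)/52 at week 8 and, by the same steps, 4(U − M)/52 at week 4.

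For scale only, a true difference of 60 units appears as 60 × 4/52 = 4.6 at week 4 and 60 × 8/52 = 9.2 at week 8. A true difference of 100 appears as 7.7 and 15.4.

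**Raw second-period values**

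- Week 8: both sequences give (36h + 8U + 8M)/52, so the between-diet contrast is zero.
- Week 4: (40h + 8M + 4U)/52 − (40h + 8U + 4M)/52 = −4(U − M)/52, so the sign is reversed.
- Second baseline: the sequences differ by 8(U − M)/52 although everyone has just spent four weeks on habitual food. This could be mistaken for carryover in diet.

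**6-month visit.** With a 26-week behavioural phase straight after diet 2, 52 − 26 = 26 weeks (50%) of the window predate it, and 16 of those are on provided diets. The monitoring section places this visit at week 49. If that is counted from first baseline, 49 − 20 = 29 weeks follow diet 2 and 23/52 (44%) predate the phase. Either way it is about half.

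**The case against.** The strongest reply is that little in the trial depends on the FFQ.

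- **UPF share.** The article assigns this to Intake24, which the team has coded to NOVA groups; no such coding is mentioned for the FFQ. Eligibility also uses 24-hour recalls. A reader might infer that the 6-month change in UPF intake will be diluted, but the documents do not support that, because Intake24 is scheduled at that visit too.
- **Adherence.** Statistical methods defines non-adherence as more than one off-diet meal a week. A frequency list cannot supply that count, whereas the food diary and weekly calls can. A reader might infer that adherence assessment as a whole is compromised. It is not: the recalls, photographs and diary match the diet periods.
- **No information at all.** A reader might conclude that the FFQ cannot measure anything on a diet, or that period 2 is confounded by the other diet. The algebra shows otherwise for change scores. The secondary outcomes are changes, a second-baseline FFQ exists, and the other diet cancels. A diluted signal remains. Mixing with the other diet affects raw period-2 values.
- **Unseen wording.** The instruction given to participants at weeks 4 and 8 is not shown and might differ from the past-year description.

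The first three replies limit the reach of the problem, and I accept them. The fourth leaves it open whether the dilution is exactly 4/52 and 8/52, but does not rescue the measure. If participants answer for recent weeks without being told to, each chooses a window, and the tool is used outside the period for which it is described. The FFQ remains a named tool for intake and adherence, with a stated window that does not fit that role.

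**Conclusion.** The point holds for FFQ-derived results. As described, week 4 and week 8 FFQs draw 7.7% and 15.4% of their window from the diet being studied. They return between-diet differences in change at 4/52 and 8/52 of the true size. Raw period-2 values mix in the other diet, and about half of the 6-month window predates the behavioural phase. These fractions rest on literal, even averaging over 52 weeks and on the article's statement of the window.

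The consequence is limited to FFQ-based dietary intake (part of a secondary outcome) and FFQ-based adherence. The primary outcome, UPF share from Intake24 and the off-diet-meal rule do not appear to be affected. The first-baseline FFQ suits habitual intake and needs no change.

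**What to change.** State that the past-year FFQ is used only for habitual intake at first baseline. Exclude the five later cross-over administrations (weeks 4 and 8 of each diet, and the second baseline) from adherence and between-diet analyses. Do not use the 6-month FFQ as the measure of change over the behavioural phase. Base these results on Intake24 (all visits), image-based assessment (weeks 4 and 8) and the food diary (on-diet periods).

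The cost is one fewer dietary measure on each diet; the recalls and photographs that remain cover two days each per assessment. If the later FFQs are also dropped from collection, participant burden falls.

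Rewording the FFQ to ask about the time since the diet began is less attractive. It departs from the validated version and, because randomisation had already started, would mix two instruments across participants or periods. The lowest response category, which is defined per month, also suits a four-week window poorly.
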